**FIGURE 2 epi470064-fig-0002:**
[figure not shown]
Study schedule.

### Data collection

3.1

PROMs will be collected at Visits 1 (baseline), 4 (2 months), and 5 (6 months) via the electronic data capture system REDCap (see Table 1 for details).^28^ Use of REDCap forced responses to progress surveys and email prompts to review data will be utilized to ensure data completeness with both participants and investigators.

**TABLE 1 epi470064-tbl-0001:** Primary and secondary objectives with corresponding outcome measures.

Primary objective	Corresponding endpoint(s)/outcome variable(s)
To investigate the diagnostic accuracy of 24/7 EEG™ SubQ Solution	Within‐participant correlation between seizure counts per month estimated from rapid clinician review of annotated 24/7 EEG™ SubQ data and ‘ground truth’ EEG seizure occurrences per month (derived from expert research team review of 24/7 EEG™ SubQ EEG data), across the 6 months of the study (‘correlation A’). Within‐participant correlation between seizure counts per month from participant‐reported seizure diary and ‘ground truth’ EEG seizure occurrences per month (derived from expert research team review of 24/7 EEG™ SubQ EEG data), across the 6 months of the study (‘correlation B’). Average difference between ‘correlation A’ and ‘correlation B’, across participants. Average difference between the number of AI‐driven automated seizure detections produced by EpiSight software and seizure counts estimated from rapid clinician review of annotated 24/7 EEG™ SubQ data, across participants. Clinician rating on the question ‘Overall, after review of annotated 24/7 EEG™ SubQ data for all participants, how would you rate your rapid clinician review?’, i.e., average score on a 10‐point Likert scale (‘the AI‐driven algorithm is very accurate compared to my rapid review’ (10) to ‘the AI‐driven algorithm is very inaccurate compared to my rapid review’ (1))

Secondary objectives	Corresponding endpoint(s)/outcome variable(s)
2 To investigate the clinical relevance of 24/7 EEG™ SubQ Solution	Change over time for average HCP questionnaires ‘Communication’, ‘Insight’ & ‘Potential of 24/7 EEG™’ scores at baseline, 2 months and 6 months
3 To investigate if the EEG data recorded with 24/7 EEG™ SubQ might be used to inform change(s) in clinical management plan for the participant	Proportion of investigators (i.e., treating clinicians) with a positive opinion, i.e., answer ‘Yes’ to the question ‘Did you adjust or change the clinical management plan during the past month?’ ‘(Yes/No)’. B Investigators rating of which data provided by 24/7 EEG™ SubQ Solution and/or clinical data led to change(s) of the clinical management plan: (i) Electrographic seizure, (ii) seizure type, (iii) seizure frequency, (iv) seizure severity, (v) cluster patterns, (vi) seizure periodicity, (vii) trigger factors, (viii) side effects of current anti‐seizure medication, (ix) lack of effects of current anti‐seizure medication, (x) non‐adherence to anti‐seizure medication, (xi) indication for adjusting or changing anti‐seizure medication, (xii) other. C Investigators rating of which adjustment(s) or change(s) to the epilepsy management plan initiated based solely or partly on data provided by 24/7 EEG™ SubQ Solution during the past month: (i) advice/education, (ii) referral, (iii) adjusting or changing anti‐seizure medication, (iv) prescription of other than anti‐seizure medication, (v) increased clinical follow‐up, (vi) changes in primary care, (vi) further examinations/test, (vii) other. D Investigators reason(s) for not changing the clinical management plan, i.e., answering ‘no’ on 3.A: (i) The patient is optimally treated (ii) Patient resistance to change in management plan despite medical, (iv) Insufficient data or information to adjust or change the clinical management plan) (v) other (free text). E Change over time for average HCP questionnaire ‘Management’ scores at baseline, 2 months and 6 months
4 To investigate participants' perception of the value of receiving feedback about seizure occurrences estimated from EEG data recorded with 24/7 EEG™ SubQ	Participants overall rating of the value of receiving feedback about seizures occurrences every month, across the full study period, from the EEG data recorded with 24/7 EEG™ SubQ i.e., average score on a 10‐point Likert scale (‘I found the feedback about when seizures had occurred according to the 24/7 EEG™ SubQ extremely helpful’) (10) to negative (‘I found the feedback about when seizures had occurred according to the 24/7 EEG™ SubQ extremely unhelpful’) (0))
5 To investigate the participants' acceptability of real‐world implementation with 24/7 EEG™ SubQ Solution	Raw score for IL01 Post market surveillance: Subject satisfaction form at 2‐months and change over time at 6‐months follow‐up
6 To investigate the participant adherence with 24/7 EEG™ SubQ Solution	Proportion of participants' percentage wear time with 24/7 EEG™ SubQ, across the study period of 6 months
7 To report the performance of 24/7 EEG™ SubQ Solution	Number of Device deficiencies during the study period (6 months)
8 To assess the quality of life with 24/7 EEG™ SubQ Solution	Change over time for average EQ‐5D‐5L scores at baseline, 2 months and 6 months. B Change over time for average Participant Weighted Quality of Life In Epilepsy (QOLIE‐31‐P) scores at baseline, 2‐months and 6 months. C Change over time for average Impact of epilepsy scores at baseline, 2‐months and 6 months. D Change over time for average Perceived Self‐Mastery Over Epilepsy scores at baseline, 2‐months and 6 months
9 To assess the health economic impact of epilepsy for participants that have used the 24/7 EEG™ SubQ Solution	Average Client Services Receipt Inventory (CSRI) scores at 6 months
10 To investigate the cost‐effectiveness of current practice and 24/7 EEG™ SubQ Solution	Quality‐adjusted life‐years (QALYs) score
11 To compare above participant reported outcome measurements (ePROM's) with historical controls obtained in previous study (10.1.4)	Endpoints 8 (A‐D) and 9 (A) compared with the 138 participants in SMILE study in the treatment‐a‐usual arm (xii)31), at baseline and 6 months follow‐up

Continuous 2 channel EEG data will be recorded from visit 3 to visit 5. To accommodate different local IT requirements, two data transfer configurations are possible whereby encrypted EEG data can either be stored within local hospital servers or stored within a third‐party cloud hosting service. The data pipeline for EEG is summarized in Figure 3. The participant will connect the external device daily via a USB cable to a tablet with a preinstalled application for data upload and recharging. Recorded EEG data will be automatically downloaded to the tablet, encrypted, and transferred via a cloud‐based data transfer application running in Microsoft Azure. The encrypted data in transit are pulled by an application (installed either at the servers of the local hospital IT network or in a 3rd‐party hosting service). Data are decrypted, stored, and made available to the investigators and treating clinicians in the UNEEG EpiSight Analyzer (EEG reading software).

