**Methods:**

Real World Testing and Cost‐effectiveness Analysis of Subcutaneous EEG (REAL‐ASE) is a UK‐based multi‐centre prospective interventional study with an expected duration of 7 months. Thirty‐three adult participants will be implanted with 24/7 EEG SubQ and collect 2‐channel EEG data for 6 months. Data will be reviewed and annotated by experts, and a summary sent to the treating clinician weekly. The treating clinician will communicate information from this annotation report to participants monthly. Changes in management can be made at the treating clinician's discretion. REAL‐ASE was approved by the Bromley Research Ethics Committee in July 2023 (reference number 23/LO/0419).

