### Sample size

2.4

We powered our study based on the primary outcome measure for diagnostic accuracy. We used data from an intracranial EEG study,^18^ which shows the correlation between the monthly number of seizure occurrences documented using participant self‐reported diary and the ground truth seizure occurrences per month, documented with the intracranial Neurovista device. The mean correlation across the group is 0.30 (SD 0.41). We seek to demonstrate a higher correlation between 24/7 EEG SubQ and the ground truth seizure occurrences. We chose a modestly higher correlation of 0.5 to power this study. At alpha 0.05, 33 participants would give 85% power to demonstrate an improvement in within‐participants correlation from 0.3 to 0.5 (calculated using G*Power).

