### Seizure detection

3.2

Continuous EEG monitoring will generate substantial data; therefore, an automated solution is required. Automated algorithms for seizure detection in multichannel EEG (reviewed by Baumgartner et al.^29^) show seizure detection sensitivity 59%–96% (median 81.4%) and false detection rate 0.08–5.38 per hour (median 0.3 per hour). The EEG analysis software AI algorithm that will be utilized (implemented within UNEEG EpiSight Analyzer) was trained using EEGs from 490 people (Temple University) and optimized on 24/7 EEG SubQ data from 32 participants. A deep neural network based on ResNet and a feature pyramid structure was designed to recognize seizures. Using 24/7 EEG SubQ data from nine PWE,^30^ a mean sensitivity of 89% and mean false positive rate 5.5/24 h was achieved. Hence, our algorithm is comparable to other multichannel EEG detection algorithms.^29^

Data will be screened by experienced neurophysiology technicians to remove suspected false positives prior to treating clinician review. Treating clinicians will be provided with annotated EEG data and a report summarizing the previous week's EEG data at weekly intervals and will have access to the continuous EEG recordings at any time.

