### Statistical analysis of primary outcome measures

4.1

The research team will review raw EEG data from 24/7 EEG SubQ to identify seizures as the ‘ground truth’. We will assess the improvement in accuracy of seizure documentation using AI‐driven algorithm with rapid expert review applied to 24/7 EEG SubQ data (‘24/7 EEG SubQ detected seizures’), compared to using self‐reported participant diary alone. We will estimate for each participant the Spearman correlation between monthly diary report and ground‐truth, and the Spearman correlation between monthly 24/7 EEG SubQ detected seizures and ground truth. We will test the hypothesis that, across the cohort, the correlation between 24/7 EEG SubQ detected seizures and ground truth is higher than between the diary and ground truth. We will also calculate for diary and 24/7 EEG SubQ detected seizures the sensitivity, specificity, false positive rate, positive predictive value, and negative predictive value, for seizure detection. We will report using Standards for the Reporting of Diagnostic accuracy studies (STARD) principles.^31^

Feasibility and acceptability will be assessed by the proportion of participants who continue in the study for >3 months of 24/7 EEG SubQ data collection.

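### Correlations A and B rest on six monthly pairs per participant, so the stated 85% power is not generally delivered at the planning values; a prespecified finer-bin analysis of outcome C would add precision at little cost

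*Protocol article*

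**What the plan says.** Table 1 (section 3.1), section 4 and section 4.1 all count seizures by the month over a six-month study. Correlation A uses "seizure counts per month estimated from rapid clinician review of annotated 24/7 EEG™ SubQ data" against the expert EEG ground truth. Correlation B uses the monthly diary count against the same ground truth. Section 4.1 makes both of them per-participant coefficients: "We will estimate for each participant the Spearman correlation between monthly diary report and" ground truth, and the same for the device. Section 4.3 compares the two with a Wilcoxon signed-rank test; their average difference is outcome C.

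Section 2.4 powers the trial on this contrast: "At alpha 0.05, 33 participants would give 85% power to demonstrate an improvement in" the within-participant correlation from 0.3 to 0.5. The benchmark is a mean monthly correlation of 0.30 with SD 0.41 in an intracranial EEG study.

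The underlying data are finer than monthly. The Abstract describes "a summary sent to the treating clinician weekly", and section 3.2 says treating clinicians receive annotated "EEG data at weekly intervals and will have access to the continuous EEG recordings at any time". The diary is electronic (section 3), and section 4.1 plans sensitivity and predictive values of the diary for seizure detection. The article describes no version of A, B or C on a unit finer than the month.

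**The concern.** A rank correlation on six points is very imprecise, and outcome C subtracts two of them. If the noise in a single six-point coefficient already matches the SD assumed for planning, little room is left for true differences between participants or for the second coefficient. The SD of the difference is then likely to exceed the planned one, and the power to fall below the figure stated. The same recordings would give about 24 to 26 weekly pairs per participant. At stake are the power of the one contrast on which the trial was sized and the width of the interval for device against diary.

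**Working it through.** **Inputs.** From section 2.4: n = 33, alpha 0.05 (sidedness not stated), planned values 0.3 and 0.5, SD 0.41. From Table 1: six monthly pairs. From section 2.3: at least 10 diary seizures per year. From section 1.1: 44% to 56% of seizures unreported. Assumptions, because the article gives no figure: true between-participant SD of B (tau) from 0 to 0.3, and 0 for A; week-to-week autocorrelation 0 or 0.5.

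**1. The plan's figure.** Standardised effect = 0.2 / 0.41 = 0.488. With n = 33:

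| Test | One-sided | Two-sided |
|---|---|---|
| Paired t | 86.4% | 77.6% |
| Wilcoxon (n × 3/π) | 84.9% | 75.5% |

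The 85% is reproduced one-sided, with 0.41 taken as the SD of the difference. But 0.41 is the SD of a single correlation. For two correlations with that SD, the SD of the difference is 0.41 × √(2(1 − r)), which equals 0.41 only if A and B correlate at r = 0.5 across participants.

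**2. Noise in one coefficient.** With no true association the SD is 1/√(n − 1): 1/√5 = 0.447 on 6 points and 1/√25 = 0.20 on 26. Simulation under bivariate normality gives:

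| True value | SD, 6 points | SD, 26 points |
|---|---|---|
| 0.3 | 0.43 | 0.19 |
| 0.5 | 0.38–0.39 | 0.16 |
| 0.9 | 0.19 | 0.06 |

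**3. Noise in the difference.** These simulations used a shared ground truth, with 24 weekly values or their six four-week means. Ranges cover both autocorrelation settings.

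| tau | SD of A − B, monthly | SD of A − B, weekly |
|---|---|---|
| 0 | 0.56–0.57 | 0.25–0.30 |
| 0.2 | 0.58 | 0.31–0.35 |
| 0.3 | 0.60–0.61 | 0.37–0.40 |

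The ratio of weekly to monthly standard error runs from 0.45 to 0.66, a cut of 34 to 55%. Sharing the ground truth helps little. At tau 0 without autocorrelation the monthly SDs of A and B are 0.384 and 0.426, and √(0.384² + 0.426²) = 0.574 against 0.559 simulated. That implies r of about 0.05, far from 0.5. For monthly B, sampling noise is 62 to 100% of the between-participant variance.

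**4. Count models.** Over-dispersed weekly counts with missed and false entries, tuned to mean B about 0.3 and mean A about 0.5, gave an SD of A − B of about 0.53 monthly and 0.27–0.30 weekly. With everyone at 10–20 seizures per year the SDs were 0.57 and 0.34. The lowest monthly value in any run near the planning values was 0.42. In an event-level model the ratio was about 0.69 at 10 true seizures per year, 0.59–0.61 at 20, and 0.50–0.58 at 50 to 150. Ten diary seizures correspond to about 10/0.56 = 18 to 10/0.44 = 23 true ones, so the realistic floor is near 20 per year.

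**5. Power on monthly counts.** Holding the mean difference at 0.2 and repeating the one-sided Wilcoxon calculation of step 1 with the SD alone changed:

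| SD of A − B | 0.2/SD | Power |
|---|---|---|
| 0.42 | 0.476 | 83% |
| 0.53 | 0.377 | 67% |
| 0.61 | 0.328 | 56% |

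Direct simulation gave 42–51% one-sided (29–38% two-sided) in the model of step 3, where six-point coefficients are also pulled towards zero (mean difference 0.418 − 0.248 = 0.17). The tuned count model, with mean difference 0.53 − 0.31 = 0.22, gave 77–78% (64–65%). Weekly counts gave 80–99% and about 99% one-sided.

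**6. If A is near 0.9 and B 0.3.** In the model of step 2 with tau 0, the mean monthly difference is 0.57 with standard error 0.080, a ratio of about 7. Power is near 100% under either unit.

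**The case against.** The monthly definition is consistent throughout and the signed-rank test on it is valid; the cost is precision only. A reader might infer that the month is arbitrary. The documents do not support that: clinicians feed results back monthly, the management questions refer to the past month, and the only benchmark is monthly. A reader might also infer that the trial is bound to be underpowered. That too fails. The 0.5 is described as a modest choice, and A compares screened, clinician-reviewed EEG with expert review of the same EEG, so a much higher value is plausible.

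The strongest point is that a weekly correlation is a different quantity. In simulations with A near 0.9, late diary entries or month-level variation in seizure rate lowered B and raised A − B: from 0.33 to 0.43 at 50 seizures per year and from 0.23 to 0.35 at 150. A weekly primary could therefore favour the device by penalising dating errors that do not affect a monthly total. This stands, and it is why replacing the monthly analysis outright is not advised.

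Two further limits stand. The resolution of diary dates is inferred from the planned detection measures, not stated. How participants who stop early enter the correlations is also not stated, so no claim is made about three-point coefficients. What does not fall is the sampling arithmetic, or its effect on the power at the plan's own values.

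**Conclusion.** The point holds as a loss of precision and an optimistic power statement, not as an invalid analysis. At the planning values the monthly SD of A − B is about 0.42 to 0.61 against the 0.41 used, so 85% is not generally delivered. How far power falls depends on the model: from slightly below 85% to about 42% one-sided. Weekly counts cut the SD by roughly 30 to 55%, least for participants with about 10 seizures per year. If A is near 0.9 the conclusion is safe either way and only the interval narrows.

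The result rests on the assumed between-participant spread and count models, and on dated diary entries. The 0.41 already contains the sampling error of its source study, whose number of months the article does not give.

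**What to change.** In Table 1 and sections 4 and 4.1, prespecify outcome C on weekly counts, with a two-week version, alongside the monthly analysis, and report all three with confidence intervals. State that the finer-bin correlations are different quantities and that a larger weekly difference is not an estimate of the monthly effect.

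- **If monthly stays primary:** restate the power in section 2.4 with an SD of A − B that includes six-point sampling error.
- **If a finer unit becomes primary:** choose it before any A or B is computed, prefer the two-week bin if late diary dating is a concern, keep monthly as supporting, and set new planning values, because the 0.30 (SD 0.41) benchmark is monthly.

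The cost is wording and analysis time. No new visits or readers are needed, and no new data provided diary entries are dated. The price is more ties and zero weeks in participants with few seizures.

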## OUTCOMES

4

The primary outcome measures of this study include: (A) Within participant correlation between seizure counts per month estimated from clinician review of annotated 24/7 EEG SubQ data (hybrid AI‐seizure detection algorithm and neurophysiology technician review) and ‘ground truth’ EEG seizure occurrences per month (derived from expert research team review of 24/7 EEG SubQ data); (B) Within participant correlation between seizure counts per month from participant reported seizure diary and ‘ground truth’; (C) Average difference between ‘correlation A’ and ‘correlation B’; (D) Average difference between the number of AI driven seizure detections and seizure counts estimated from rapid clinician review of annotated 24/7 EEG SubQ data (clinician inspection of data), across participants; and (E) Clinician rating of accuracy (compared to their own review) of annotated 24/7 EEG SubQ data.

A complete list of primary and secondary objectives with corresponding outcomes can be found in Table 1.

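### Primary outcome E names three different things to rate (the clinician's own review, the AI, and the technician-screened annotations), so its score has no single meaning and cannot support a conclusion about the AI alone

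*Protocol article*

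**What the plan says.** Table 1 (section 3.1) lists outcome E under the primary objective of diagnostic accuracy and prints the item in full. The question, put after the clinician has reviewed annotated data for all participants, is "how would you rate your rapid clinician review". The top of the 10-point scale reads "the AI‐driven algorithm is very accurate compared to my rapid review", and the bottom is its opposite.

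Section 4 (Outcomes) lists E among the primary outcome measures as "Clinician rating of accuracy (compared to their own review) of annotated 24/7 EEG SubQ data". Under outcome A, the same section describes the annotated data as "hybrid AI‐seizure detection algorithm and neurophysiology technician review".

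Section 3.2 (Seizure detection) sets the order of work: "Data will be screened by experienced neurophysiology technicians to remove suspected false positives prior to treating clinician review". It then says that treating clinicians receive the annotated data with a weekly report and "will have access to the continuous EEG recordings at any time". For the algorithm alone, in SubQ data from nine people, it reports that "a mean sensitivity of 89% and mean false positive rate 5.5/24 h was achieved".

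**The concern.** A rating scale needs one object. Here a respondent who follows the question rates their own reading. One who follows the end points rates the algorithm. A reader of section 4 will take the result as a rating of the AI-plus-technician product. Once the scores are collected, no analysis can recover which object each clinician had in mind.

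The order of work adds a second difficulty. If the score is taken as its end points say, clinicians judge the algorithm from material that technicians have already cleaned.

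The discussion section treats inadequacy of the algorithm in clinicians' eyes as a real risk to feasibility, and E is the only listed outcome that asks clinicians directly about the algorithm's accuracy. A high mean could be reported as clinicians endorsing the AI when it reflects the screening, or the clinicians' confidence in their own reading.

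**Working it through.** **Step 1: the wordings side by side.**

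| Place | Object rated | Compared with |
|---|---|---|
| Table 1, question | The clinician's own rapid review | Not stated |
| Table 1, scale end points | The AI algorithm | The clinician's rapid review |
| Section 4, outcome E | Annotated data (AI plus technician) | The clinician's own review |

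No two rows agree. The clinician's review is the object in the first row and the comparator in the other two. The last two rows differ by the technician step.

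**Step 2: which reading the screening affects.** Section 3.2 puts the removal of suspected false positives before clinician review. Under the section 4 definition, that removal is part of what is rated, so it causes no bias. Under the end points' definition, it is a correction made by people other than the object rated, and it favours the AI.

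**Step 3: how large the screening task is.** The plan gives no figure for E, so there is none to reproduce. The inputs are:

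- sensitivity 0.89 and 5.5 false positives per 24 h (section 3.2)
- at least 10 diary seizures a year at entry (section 2.3)
- 6 months of recording
- 10 and 30 seizures a month, which are assumptions and appear nowhere in the plan

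False positives are 5.5 × 7 = 38.5 a week, 5.5 × 30 = 165 per 30 days, and 5.5 × 182.5 ≈ 1,004 per participant over 6 months at full wear (about 502 at an assumed 50% wear).

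For s seizures per 30 days, raw AI positive predictive value (PPV) = 0.89s / (0.89s + 165). Wear time cancels if seizures and false alarms fall in proportion.

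| Seizure rate | s | True detections | PPV | False share |
|---|---|---|---|---|
| 10 a year (entry minimum) | 0.83 | 0.74 | 0.74/165.74 = 0.4% | 99.6% |
| 10 a month (assumed) | 10 | 8.9 | 8.9/173.9 = 5.1% | 94.9% |
| 30 a month (assumed) | 30 | 26.7 | 26.7/191.7 = 13.9% | 86.1% |

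The entry minimum is a diary count, and section 1.1 cites 44% to 56% of seizures going unreported. On that basis 10 diary seizures would mean 10/0.56 = 17.9 to 10/0.44 = 22.7 true seizures a year, and a PPV of about 0.8% to 1.0%.

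**Step 4: what the clinician might see.** Suppose, as an assumption, that technicians removed 99% of false alarms and no true detections. False positives fall to 1.65 per 30 days, and the PPV in the three rows becomes about 31%, 84% and 94%. Raw and screened output would then look very different. How a clinician would turn that difference into points on a 1 to 10 scale cannot be derived from the document.

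**The case against.** The strongest defence has four parts.

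- **Bias needs a defined target.** Under section 4 the technician step belongs to the product being rated. A reader might infer that the score is biased upward whatever the reading. The document does not support that: the upward direction follows only if the score is taken as a rating of the AI. This part stands.
- **Clinicians are not confined to the screened annotations.** They have the continuous EEG at any time, and the article does not say whether rejected detections stay visible in the reading software. The removed events are only suspected false positives, so some false alarms may remain and some true seizures may be lost. A reader might infer that clinicians cannot see the AI's errors, and the text does not establish this. It stands as a limit. Equally, nothing says that unscreened detections are shown when the rating is given, and the question itself refers to annotated data.
- **The PPV figures are not a measure of the effect.** They describe the raw algorithm and not a shift in the score. The upper rates are assumed, section 2.3 sets no maximum seizure rate, and 5.5 per 24 h is a mean from nine people. This stands, so the figures serve only for scale.
- **The consequences are limited.** The sample size rests on the correlations, Likert items are summarised descriptively (section 4.3), and outcome D also addresses the AI. All true, but D does not repair E, and a descriptive summary of an item with three possible objects still has no clear meaning.

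**Conclusion.** The mismatch is established from the text: the question, the end points and section 4 name three different objects for one listed primary outcome. Collected as written, the mean of E has no single interpretation.

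That the score would flatter the AI is a probable inference and not a measured effect. It holds if the score is read as its end points say and clinicians rate mainly from the screened annotations. Its size on the scale is unknown. The screening it depends on is substantial: about 86% to 99.6% of raw detections would be false across the rates from 30 a month down to 10 a year, given the stated algorithm performance.

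The damage is confined to the interpretation of E. The powered comparison of correlations A and B is not affected. The mismatch also does not in itself require E to lose its primary status. That would be a matter of preference, since aligning the wording removes the fault.

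**What to change.** Reword the Table 1 question and end points so that both rate the annotated report (AI plus technician screening) against the clinician's own review, and keep section 4 in the same terms. Add a sentence that E supports no conclusion about the AI alone.

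If a statement about the AI alone is wanted, there are two routes:

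- Use outcome D, specifying that AI detections are counted before technician screening.
- Add an analysis of AI-alone sensitivity and false positive rate against the existing ground truth.

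The second must be stated as new. Section 4.1 plans such accuracy measures only for the diary and for the AI combined with rapid expert review, so no AI-alone result of that kind is currently planned.

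The cost is one questionnaire item and matching text in Table 1 and section 4, plus a modest extra analysis if the second route is taken. Scores already collected under the present item would have to be reported separately and not pooled with later ones.

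### Endpoint 3A counts any management change, per investigator, as a positive opinion, so the proportion for objective 3 includes changes unrelated to SubQ

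*Protocol article*

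**What the plan says.** All of this is in the protocol article, Table 1 (section 3.1, Data collection), under secondary objective 3, unless another place is named.

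- **Objective 3:** whether SubQ EEG data "might be used to inform change(s) in clinical management plan for the participant".
- **3A:** "Proportion of investigators (i.e., treating clinicians) with a positive opinion", where a positive opinion means answering 'Yes' to "Did you adjust or change the clinical management plan during the past month".
- **3B:** "Investigators rating of which data provided by 24/7 EEG™ SubQ Solution and/or clinical data led to change(s) of the clinical management plan". The options include medication side effects and non-adherence.
- **3C:** the kinds of change "initiated based solely or partly on data provided by 24/7 EEG™ SubQ Solution during the past month".
- **3D:** reasons for a 'No' on 3A, one of which is "The patient is optimally treated".
- **3E:** change over time in the 'Management' questionnaire scores.

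Section 4.2 describes this group of outcomes as resting on input from the SubQ recordings and says they will be assessed by questionnaire. The study is non-randomised (section 2.1). Objective 11 limits the historical-control comparison to endpoints 8 and 9.

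**The concern.** The objective and the proportion attached to it measure different things. The objective concerns changes informed by SubQ. The 3A question asks about any change, for any reason, and a 'Yes' is then labelled a favourable opinion. A clinician who changed the plan on clinical grounds alone, without using the recording, is counted as positive.

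The units also differ. Objective 3 refers to the participant and 3D to the patient, but 3A divides by investigators. A clinician with several participants can give different answers for each, and different answers each month.

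Participants have at least 10 seizures a year (section 2.3), receive feedback from their clinician at least monthly (section 3), and may have their management changed at the clinician's discretion (Abstract, Methods). Some changes unrelated to the device are to be expected. With no comparator, they cannot be separated from changes due to SubQ. At stake is whether this proportion can be read as evidence that SubQ informs care.

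**Working it through.** The article gives no expected value, background rate or precision for 3A, so there is no stated figure to reproduce. The check asks what 3A would show if SubQ had no effect on management.

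**Inputs from the document:** 33 participants (section 2.1); 6 months of recording with at least monthly clinician contact (section 3); a question that looks back one month (3A).

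**Assumed inputs, because the document gives none:** *p*, the chance of a management change in one participant-month without any device effect, taken as 5%, 10% and 20%; *k*, the participants per investigator, taken as 1 and 3; independence between months and participants.

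**Reading 1: each participant-month is one answer.** The expected proportion is *p* itself: 5%, 10% or 20%. With complete follow-up there are 33 × 6 = 198 participant-months. That gives about 10 (198 × 0.05), 20 (198 × 0.10) or 40 (198 × 0.20) positive answers with no device effect.

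**Reading 2: one month, and an investigator is positive if any of *k* participants had a change.** The formula is 1 − (1 − *p*)^*k*. For *k* = 3:
- *p* = 5%: 1 − 0.95³ = 14%
- *p* = 10%: 1 − 0.90³ = 27%
- *p* = 20%: 1 − 0.80³ = 49%

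**Reading 3: an investigator is positive if they answered 'Yes' at least once over 6 months.** The formula is 1 − (1 − *p*)^(6*k*).

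| *p* per month | *k* = 1 (exponent 6) | *k* = 3 (exponent 18) |
|---|---|---|
| 5% | 27% | 60% |
| 10% | 47% | 85% |
| 20% | 74% | 98% |

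**Comparison with an attributed count.** If only changes attributed at least partly to SubQ were counted, the expected value with no device effect would be about 0%, apart from misattribution.

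Under every reading 3A is above zero when the device does nothing. How far above depends on the aggregation rule and on caseload.

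**The case against.** The strongest reply is that 3A is a filter question. It is one of five endpoints listed under objective 3, none of them ranked. A 'No' leads to 3D, and changes are characterised in 3B and 3C. A neutral opening question followed by attribution is ordinary questionnaire design, and 3C is restricted to changes "initiated based solely or partly on data provided by 24/7 EEG™ SubQ Solution". Attribution is therefore present in objective 3 as a whole. How monthly answers are combined may be set out in a full protocol or SAP that is not shown, so the absence of such a rule is not a finding. The objective is secondary and tentatively worded, and section 4.3 sets no success threshold for it.

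Most of this stands. It means that two stronger readings, which a reader might infer, are not supported:

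- **That 3A is the headline result for objective 3.** The document ranks nothing.
- **That 3A will approach 100% without any device effect.** This needs an ever-'Yes' rule over 6 months, several participants per investigator and a sizeable background rate. With five participants and rates of 10% or 20%, the Reading 3 formula gives 96% or 99.9%. None of these conditions is stated, and a participant-month count would simply equal the background rate.

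The reply does not reach the definition itself. 3A is more than a filter in the text: it is listed as an endpoint, it is the only proportion defined under objective 3, and 'Yes' is explicitly scored as positive. 3B expects some changes to come from clinical data. 3C describes the type of change and leaves what 3A counts unchanged.

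**Conclusion.** The concern holds as a mismatch between an endpoint and its objective. As worded, 3A mixes changes informed by SubQ with background changes, uses a unit that does not fit the participant-level objective or 3D, and has no comparator to remove the background.

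With zero device effect it would show 5–20% per participant-month, or 27–74% (one participant) to 60–98% (three participants) per investigator ever answering 'Yes' over 6 months. These ranges illustrate the size of the problem and are not predictions. They rest on assumed monthly rates of 5–20%, assumed caseloads and independence.

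The consequence is moderate: one of several endpoints for one secondary objective, with the attributed information already planned for collection in 3C. The definition should still be corrected, because as it stands the proportion does not answer the question that objective 3 asks.

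**What to change.** 1. Define the proportion for objective 3 as the share of participants, and of participant-months, with at least one change attributed solely or partly to SubQ in 3C.
2. Report it with an interval that allows for clustering by participant and by clinician.
3. Keep the present 3A question as the filter for 3D and as a descriptive all-cause change rate beside the attributed one, without the positive-opinion label.
4. State as a limitation that 3C is self-attribution by unblinded treating clinicians, and that 'partly' is a permissive criterion.

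The cost is a wording change in Table 1 and the matching analysis text. No new question is needed, provided each completed form can be linked to a participant and a month, which the wording of 3C and 3D suggests. The reported proportion will be lower than under 3A. Misattribution could still inflate it, so the change removes the unattributed background but does not make the measure objective.
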